### 3.3. Sample Size

#### 3.3.1. Sample Size for Periodontitis and Incidence of Hypertension

The projected sample size for periodontitis and incidence of hypertension will be 1212 individuals from those participating in the umbrella cohort. A logistic regression (LR) for a binary response (hypertension) on an independent variable (periodontitis) with a sample size of 866 participants (90% of whom are in group X = 0 and 10% are in group X = 1) achieves 90% power with 0.05 significance to detect a change in the Probability (Y = 1) of an estimated value of incidence of hypertension of 21.5%. This change corresponds to a Relative Risk (RR) of 2.4 (a RR between 1 and 2.74 has been reported) (6, 30, 36). An adjustment was made since the multiple regression of the variable of interest in the other independent variables in the LR obtained a *R*^2^ of 0.3. A 40% dropout rate is expected (*n* = 346), so the projected sample size will be 1,212 people.

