## 1. Introduction

High blood pressure (HBP) is the leading risk factor for myocardial infarction, cerebrovascular events, atherosclerosis, aortic aneurysms, peripheral arterial disease, heart failure, and chronic kidney disease, among other ailments. Hypertension (high blood pressure) is the most important cause of premature morbidity and mortality and has become a major public health problem (1). Almost 45% of the worldwide population is affected by it and the estimate increases with age in both sexes (2, 3). The etiology of most HBP is multifactorial, resulting from the interaction of renal, neural, cardiac, vascular, and endocrine mechanisms under the influence of genetic, epigenetic, as well as environmental, lifestyle and social factors (4). Additionally, pathophysiological alterations related to microbial dysbiosis, chronic inflammatory states, endothelial dysfunction, increased peripheral vascular resistance, oxidative stress, and immune system responses have been also associated to the incidence and prevalence of hypertension (5–8).

Periodontitis, in turn, is the most common periodontal disease (PD) in adults. Periodontitis has a high prevalence worldwide, it is known to affect around 30–50% of the population in developed countries (9). Periodontitis is a chronic inflammatory disease of infectious origins that has drawn increasing attention as a risk factor to develop hypertension and cardiovascular disease (CVD) (10, 11). Periodontitis is characterized by host-mediated microbe-associated inflammation that results in progressive destruction of the structures that support the teeth (gingiva, cementum, periodontal ligament, and alveolar bone), often leading to tooth loss (3). In particular, the role of the subgingival microbiota in the development of periodontitis, has been clearly identified (12, 13).

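### The sample-size inputs cannot all hold: with the R-squared adjustment, a relative risk of 2.4 does not give 866, so either the adjustment is not in 866 or 2.4 is not a relative risk

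*Protocol article*

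**What the plan says.** Section 3.3.1 bases the calculation on a logistic regression of hypertension on periodontitis "with a sample size of 866 participants (90% of whom are in group X = 0 and 10% are in group X = 1"), which "achieves 90% power with 0.05 significance". The quantity to be detected is a change in the probability of hypertension, tied to "an estimated value of incidence of hypertension of 21.5" per cent. The text then adds: "This change corresponds to a Relative Risk (RR) of 2.4".

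After that comes the covariate adjustment, with an R-squared of 0.3: "An adjustment was made since the multiple regression of the variable of interest in the other independent variables in the LR". Finally, 40% of 866 (346) is added for dropout, giving 1,212.

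The section does not give the risk in each group, the sidedness of the test, or the sample size before the adjustment. The first hypothesis in section 2.3 is covariate-adjusted (sex, age, smoking, oral hygiene, education, occupation, marital status), so the R-squared term matters for it. Section 9.1.2 puts mild, moderate and severe periodontitis together in the exposed group.

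**The concern.** The section prints a full set of inputs and a result, so the result can be checked. An R-squared of 0.3 divides the unadjusted size by 0.7, an increase of 43%. If 866 already contains that increase, the unadjusted size was about 606 (866 × 0.7). If it does not, the stated 90% power describes an unadjusted comparison and not the hypothesis in section 2.3.

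The 1,212 is built directly on 866, so a reader cannot tell what power the study has for its stated hypothesis until the inputs are reconciled.

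**Working it through.** **Inputs (section 3.3.1).** Exposed share B = 0.10; significance 0.05, taken as two-sided because sidedness is not stated; power 90%; R² = 0.3; effect 2.4; incidence figure 21.5%, group not stated.

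**Formula (Hsieh-Bloch-Larsen, binary covariate).** With P = (1−B)p0 + B·p1:

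N = [1.960·√(P(1−P)/B) + 1.2816·√(p0(1−p0) + p1(1−p1)(1−B)/B)]² / [(p1−p0)²(1−B)], then N/(1−R²) = N/0.7.

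**Step 1. Relative risk 2.4, as printed.**

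| What 21.5% denotes | p0 | p1 | N unadjusted | N with R² = 0.3 |
|---|---|---|---|---|
| Risk in exposed | 8.96% | 21.5% | 864 | 1,235 |
| Risk in unexposed | 21.5% | 51.6% | 266 | 380 |
| Overall risk | 18.9% | 45.3% | 326 | 466 |
| Risk difference | 15.4% | 36.9% | 438 | 625 |

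The last column never gives 866.

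**Step 2. Reading (a): 866 without the adjustment.** p0 = 0.215/2.4 = 0.0896 and P = 0.1021. The two square roots are 0.9576 and 1.2651, and the denominator is 0.01416.

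N = (1.8768 + 1.6213)²/0.01416 = 864, within 0.2% of 866. If R² = 0.3 is then applied, 866 counts as 866 × 0.7 = 606, and power = Φ[(√(606.2 × 0.01416) − 1.8768)/1.2651] = Φ(0.83) = 79.7%.

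**Step 3. Reading (b): 866 with the adjustment.** Take 2.4 as an odds ratio and 21.5 points as the change. With p0 = 0.395, p1 = 2.4 × 0.395/(1 + 1.4 × 0.395) = 0.610, a change of 21.5 points. P = 0.4165, the square roots are 1.5590 and 1.5425, and the denominator is 0.04177.

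N = (3.0555 + 1.9768)²/0.04177 = 606, and 606.3/0.7 = 866. The relative risk is 0.610/0.395 = 1.55. The match does not depend sharply on the baseline: for p0 from 0.35 to 0.405 the adjusted size stays between 865 and 868.

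**Step 4. Other variants.**
- Odds ratio 2.4, two-sided, adjusted: 1,618 (21.5% in the exposed), 1,007 (unexposed) or 1,050 (overall).
- One-sided 0.05, odds ratio 2.4, 21.5% overall, adjusted: 867. The relative risk is then 1.88.
- One-sided 0.05, relative risk 2.4, 21.5% in the exposed, adjusted: 1,031 by the formula above, or 851 by a Wald log-odds formula. The latter is near 866 but not equal to it.

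**Step 5. Power at the expected number of completers.** 1,212 × 0.6 = 727, which counts as 727 × 0.7 = 509 after the adjustment.
- Risks of (a): Φ[(√(508.9 × 0.01416) − 1.8768)/1.2651] = Φ(0.64) = 74%.
- Risks of (b): Φ[(√(508.9 × 0.04177) − 3.0555)/1.5425] = Φ(1.01) = 84%.

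**Step 6. Sensitivity to the exposed share** (727 completers, R² = 0.3, two-sided).

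| Exposed share | Power, risks of (a) | Power, risks of (b) |
|---|---|---|
| 10% | 74% | 84% |
| 20% | 90% | 98% |
| 30% | 96% | 99% |
| 50% | 98% | >99% |

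**The case against.** The strongest reply is reading (b). The text describes 21.5% in terms of a change in probability, a logistic regression estimates an odds ratio, and the article says outright that an adjustment was made. On that reading the split, power, two-sided 0.05, 21.5 points, 2.4 and R² = 0.3 all fit 866, and only the label on 2.4 is wrong. Reading (a) has to assume that 21.5% is the exposed-group risk, which the text never says, and that the adjustment sentence is untrue.

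This stands against the stronger inference a reader might draw: that the adjustment was left out, that 1,235 participants are needed and that 866 gives only 80% power. Those figures hold under reading (a) alone. It does not rescue the paragraph as printed. Under (b) the relative risk is about 1.5, and the risks of roughly 39.5% and 61% appear nowhere in the article.

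A reader might also take the 10% exposed share to be contradicted by the Introduction, which says of periodontitis that "it is known to affect around 30–50% of the population in developed countries". That figure is for developed countries, while this cohort is clinically healthy, aged 20 to 50, and excludes diabetes and rapidly progressing periodontitis. It does not by itself contradict 10%. Because the exposed group takes in any severity, a higher share is possible, and it would raise power.

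That a journal article condenses the full protocol is no answer here, because the point disputes a result the article prints.

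**Conclusion.** The calculation in section 3.3.1 is wrong as written. No two-sided reading tried with a relative risk of 2.4 and R² = 0.3 gives 866. Either the adjustment is not in 866, or 2.4 is an odds ratio labelled as a relative risk; the one-sided match at 867 also needs the second. The document does not show which.

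The practical size is the gap between the printed 90% and the adjusted power at about 727 completers: about 74% on the risks of (a) and 84% on those of (b). This assumes the binary-covariate logistic formula, a two-sided 0.05 test, 10% exposed and the article's own 40% loss. It is not a finding that the study is underpowered: if the exposed share is 20% or more, power at 727 is 90% or higher on either pair of risks.

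**What to change.** Re-run and restate the paragraph with:
- the risk in each group (p0 and p1), and what 21.5% denotes;
- whether 2.4 is a relative risk or an odds ratio;
- one- or two-sided 0.05;
- the size before and after dividing by 0.7;
- the resulting power at about 727 evaluable participants, in place of 90% at 866;
- a sensitivity range for exposed shares above 10%, since the exposed group includes any severity.

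The cost is about an hour of calculation and one corrected paragraph. Enrolment stays at 1,212; only the stated power and the labels change. If 10% exposed proves right, the lower power should be acknowledged.

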## Abstract

Cardiovascular diseases are the leading cause of morbidity and mortality worldwide. High blood pressure in particular, continues to increase throughout the global population at an increasingly fast pace. The relationship between arterial hypertension and periodontitis has been recently discussed in the context of its origins and implications. Particularly relevant is the role of the periodontal microbiome linked to persistent local and systemic inflammation, along with other risk factors and social determinants of health. The present protocol will investigate/assess the association between periodontal disease and its microbiome on the onset of hypertension, within a cohort from Mexico City. One thousand two hundred twelve participants will be studied during a 60-month period. Studies will include analysis of periodontal conditions, sampling and sequencing of the salivary and subgingival microbiome, interviews on nutritional and lifestyle habits, social determinants of health, blood pressure and anthropometric measurements. Statistical associations and several classic epidemiology and machine learning approaches will be performed to analyze the data. Implications for the generation of public policy—by early public health interventions or epidemiological surveillance approaches—and for the population empowerment—via the establishment of primary prevention recommendations, highlighting the relationship between oral and cardiovascular health—will be considered. This latter set of interventions will be supported by a carefully planned science communication and health promotion strategy. This study has been registered and approved by the Research and Ethics Committee of the School of Dentistry, Universidad Nacional Autónoma de México (CIE/0308/05/2019) and the National Institute of Genomic Medicine (CEI/2020/12). The umbrella cohort was approved by the Institutional Bioethics Committee of the National Institute of Cardiology-Ignacio Chavez (INC-ICh) under code 13-802.

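### The 40% dropout allowance is added to 866 rather than divided out, so 1,212 recruits leave about 727 completers and the stated 90% power is not delivered

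*Protocol article*

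**What the plan says.** All the figures stand in one paragraph of the protocol article, section 3.3.1.

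- The calculation is for a logistic regression of hypertension on periodontitis, "with a sample size of 866 participants (90% of whom are in group X = 0 and 10% are in group X = 1".
- This size "achieves 90% power with 0.05 significance". Whether the test is one- or two-sided is not stated.
- The outcome input is "an estimated value of incidence of hypertension of 21.5" per cent, and "This change corresponds to a Relative Risk (RR) of 2.4".
- The text reports an adjustment for an R-squared of 0.3 between periodontitis and the other covariates.
- The dropout step is: "A 40% dropout rate is expected (*n* = 346), so the projected sample size will be 1,212 people".

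The same section opens with the total: "The projected sample size for periodontitis and incidence of hypertension will be 1212 individuals". The Abstract repeats it: "One thousand two hundred twelve participants will be studied during a 60-month period". Nowhere does the article define the 40% as a share of completers.

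**The concern.** A dropout rate is a fraction of the people enrolled. If a required number of completers is multiplied by 1 plus the rate, instead of being divided by 1 minus the rate, enrolment comes out too small. At 40% the gap between the two is large. The printed 346 shows which calculation was done.

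This is the article's only power calculation. Section 3.3.2 sizes the microbiome work by a lower bound for network inference, not by power. The calculation supports objective (ii) in section 2.1 and the first hypothesis in section 2.3. At stake is whether the power claim is true at the plan's own loss rate. With 10% exposed, the expected number of participants with periodontitis falls from about 87 (10% of 866) to about 73 (10% of 727), if loss is even across the groups.

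**Working it through.** **Inputs (all from section 3.3.1).** Required n = 866; dropout 40%, given as 346; total 1,212; 10% exposed; 90% power; alpha 0.05; incidence 21.5%; RR 2.4; R-squared 0.3.

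**Step 1: reproduce the plan's total.** 0.40 × 866 = 346.4, printed as 346. 866 + 346 = 1,212. The total is therefore 866 × 1.4.

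**Step 2: apply the stated loss to the stated enrolment.**
- 1,212 × (1 − 0.40) = 727.2, so about 727 completers.
- 866 − 727 = 139, and 139 / 866 = 16%.
- Loss at which 1,212 leaves 866: 1 − 866 / 1,212 = 28.5%.
- Enrolment for 866 completers at 40% loss: 866 / 0.6 = 1,443.3, so 1,444, which is 232 more than 1,212.

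The figures 866, 40% and 1,212 cannot all hold.

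**Step 3: power at 727, taking 90% at 866 as given.** Power = Φ((z_α + z_β) × √(727/866) − z_α).
- Two-sided: Φ((1.960 + 1.282) × √(727/866) − 1.960) = Φ(1.010) = 84.4%.
- One-sided: Φ((1.645 + 1.282) × √(727/866) − 1.645) = Φ(1.036) = 85.0%.

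**Step 4: can the 866 itself be reproduced?** The text does not say which group the 21.5% belongs to. Assume it is the exposed group, with a two-sided test:
- p1 = 0.215; p0 = 0.215 / 2.4 = 0.0896; difference d = 0.1254.
- Pooled P = 0.9 × 0.0896 + 0.1 × 0.215 = 0.1021.
- A = √(P(1 − P) / 0.09) = 1.0094.
- B = √(p0(1 − p0)/0.9 + p1(1 − p1)/0.1) = 1.3336.
- n = (1.960 A + 1.282 B)² / d² = 864, close to the printed 866.
- Power = Φ((d√n − 1.960 A) / B) = 90.0% at 866 and 85.4% at 727.

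This match leaves the R-squared out. The usual adjustment divides n by 1 − 0.3, giving 864 / 0.7 = about 1,235. Equivalently, it multiplies the effective n by 0.7:

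| Completers | Power without R-squared | Power with R-squared 0.3 |
|---|---|---|
| 866 | 90.0% | 79.7% |
| 727 | 85.4% | 73.8% |

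**Step 5: other readings.** One alternative reproduces 866 with the adjustment included: one-sided, 21.5% as overall incidence, and 2.4 taken as an odds ratio. It needs 867 and gives 85.4% at 727, but the text calls 2.4 a relative risk. Taking 21.5% as the unexposed or overall incidence with RR 2.4 leaves power above 90% at 727, but those readings do not reproduce 866.

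**The case against.** The inflation slip is hard to defend; the fair objections concern its consequences.

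**The power figure.** A reader might infer that the study has about 84% power on its stated inputs. The article does not support that. The 84–85% comes either from trusting that 866 gives 90%, or from a calculation that omits an adjustment the article says was made. A reader might equally infer that the true power is 74%. That is not established either: it rests on one reading of an ambiguous 21.5%, and another reading reproduces 866 with the adjustment. This objection stands, so the power must be given conditionally.

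**Severity.** Taking 90% at 866 as given, the loss is 5 to 6 points and power stays above 80%. No design feature, endpoint or analysis changes. This stands, and the point is a correction of reporting. One might infer that 232 more people must be recruited, but 1,444 is only the number that would match 866 completers at 40% loss.

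**Standing of the analysis.** Section 2.1 names the microbiome association as the primary endpoint and lists the periodontitis–hypertension relationship among the secondary goals. Nothing in the article ties the reading of a null result to exactly 90% power, so it would go too far to say that a null result will be over-interpreted.

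**Who counts as lost.** Under sections 3.4.3 and 3.6.1.2, participants who develop hypertension and start regular therapy are eliminated, although their outcome is already known. Six-monthly contacts also collect diagnoses. Section 3.3.1 does not say whether the 40% includes such people, so 727 may understate those with a usable outcome. This makes 727 less certain but does not repair the arithmetic, because 1,212 was derived from 866 and 40% alone.

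**Conclusion.** The error holds. The dropout allowance multiplies by 1.4 where it should divide by 0.6. At the stated 40% loss, 1,212 enrolled leave about 727 completers, 16% short of the 866 on which the 90% power rests, so that power is not delivered as claimed. The head-count uses only three printed figures and does not depend on how the 21.5%, the RR or the sidedness is read. It does assume that the 40% is a share of those enrolled and that those lost do not enter the logistic regression.

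The size of the power loss is less certain. It is about 5 to 6 points, to 84–85%, if 866 truly gives 90% and loss is even across the exposure groups. Whether 866 gives 90% with the R-squared adjustment is open: on the reading that comes closest with a two-sided test and a relative risk, it does not. The correction should be made, but the point does not call the design into question.

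**What to change.** Keep enrolment at 1,212 and correct the last step of section 3.3.1 to say that:

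- 40% loss from 1,212 leaves about 727 evaluable participants;
- 1,212 yields 866 completers only if loss is at most 28.5%;
- 866 completers at 40% loss would need 1,444 enrolled;
- power at 727 is about 84–85%, conditional on 866 giving 90%.

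Before printing the power figure, recompute it with the R-squared of 0.3 included, and state which group the 21.5% refers to and whether the test is one- or two-sided. If the two-sided reading of 8.96% against 21.5% is the intended one, the figures to report are about 80% at 866 and 74% at 727.

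The cost is a sentence or two, one recalculation from inputs the authors already hold, and a less favourable power statement. The enrolment figure of 1,212 in the Abstract and at the start of section 3.3.1 can stay, and no extra recruitment is needed.

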#### 3.3.2. Sample Size for the Microbiological Studies

The sample size of the oral and subgingival microbiome study is projected to be 200 people sub-sampled in a randomized adjusted cohort design (100 subjects with periodontitis and 100 without periodontitis). This is so since the lower bound for the number of samples to probabilistically infer co-existence networks (in this case of microbial species) by the method we use (based on the calculation of the mutual information function) is ~100 per evaluated group (37). A total of 400 microbial samples per evaluation time (baseline and 60 follow-up months) will be placed 200 for periodontal health subjects and 200 for periodontitis subjects, with a subdivision of 100 for saliva and 100 subgingival samples each. Since the sequencing analysis for microbiota is relatively expensive it was decided to use just this number for experimental design. Sampling for microbiome analysis will be done in participants who have developed hypertension (with periodontitis and without periodontitis) and in those who have remained at normal blood pressure levels (with periodontitis and without periodontitis).

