## 2. Scope of the Project

### 2.1. Main Goal of the Study

The main objectives of this study are: (i) to identify the subgingival microbiome, as well as the factors associated with periodontitis, (ii) to quantify its association with the incidence of hypertension and (iii) to analyze the triple association between the oral subgingival microbiome, the presence and extent of periodontal disease, and the development of hypertension in people aged 20 years and over that will be followed for a period of 60 months.

The primary endpoint is to determine the association of the subgingival microbiome profiles with the presence of hypertension and periodontitis. Secondary goals include the assessment of the relationship between periodontitis and hypertension in the socio-demographic context of the metropolitan population of Mexico City, as well as the characterization of the subgingival microbiome in periodontal health and periodontitis conditions of such study sample.

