### 5.1. Methods Collection

Sampling of saliva and subgingival plaque will be performed at baseline and at the end of follow-up in the participants selected for the oral microbiome analysis. All participants will be asked to stop taking antibiotics 3 months before and to stop mouthwashes—1 week before the clinical examination. History of occasional antibiotic consumption (outside sampling dates) will be recorded and analyzed. They will also be asked to stop tooth brushing 24 h before the clinical exam. They will be asked to refrain from eating, drinking anything other than water and chewing gum for 12 h prior to taking samples (76).

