#### 9.2.4. Design of the Association Studies of the Microbiome With Clinical, Social Variables, and Risk Factors

In order to determine the relationships between the oral subgingival microbiome with response variables (clinical, biochemical, socioenvironmental, lifestyle, among other risk factors) a hybrid design has been chosen that combines classic approaches to epidemiology and biomedical statistics (proportional hazards models, Cox regressions, multivariate and logistic, transformed variables, etc.) with contemporary analysis methodologies based on computational learning ideas (neural networks, deep learning, support vector machines, Bayes naive-type models, decision trees, etc.). The choice between models will consider principles of maximum likelihood and maximum parsimony.

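### Section 3.3.2 gives two unreconciled rules for choosing the 200 microbiome participants, and the one based on hypertension outcome cannot select anyone for baseline sampling

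*Protocol article*

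**What the plan says.** Section 3.3.2 of the protocol article sets the size of the microbiome study at "200 people sub-sampled in a randomized adjusted cohort design (100 subjects with periodontitis and 100 without periodontitis". It counts the specimens accordingly: "A total of 400 microbial samples per evaluation time (baseline and 60 follow-up months", shared equally between the two periodontal groups, "with a subdivision of 100 for saliva and 100 subgingival samples each". The justification is a lower bound of about 100 samples per evaluated group for inferring microbial co-existence networks.

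The last sentence of the same section names a different basis: "Sampling for microbiome analysis will be done in participants who have developed hypertension (with periodontitis and without periodontitis", and also "in those who have remained at normal blood pressure levels (with periodontitis and without periodontitis". It gives no counts, sampling fractions or timing, and does not link this sentence to the 100 + 100 draw.

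Three other places bear on it:

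- Section 3.4.1 requires participants to be free of hypertension at entry.
- Section 5.1 says that saliva and plaque sampling "will be performed at baseline and at the end of follow-up in the participants selected for the oral microbiome analysis".
- Section 4 describes the appointment for those who accept the invitation as including saliva and subgingival sampling, with no restriction to a selected subset.

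The subsample serves the primary endpoint in Section 2.1 (microbiome profiles against hypertension and periodontitis) and the objective "to analyze the triple association between the oral subgingival microbiome, the presence and extent of periodontal disease, and the development of hypertension". A specific goal in Section 2.2 relates the baseline microbiome to 60-month incidence of hypertension.

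**The concern.** The two rules produce different samples. Drawing on periodontitis is an exposure-based cohort sample: it can be done at baseline, and hypertension is left to occur. Drawing on hypertension crossed with periodontitis is outcome-dependent: it can be done only after follow-up.

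At stake are the specimens themselves. Baseline plaque and saliva not taken from a person who later becomes hypertensive cannot be obtained afterwards, so an analysis plan could not repair the wrong choice. The rule also decides which quantities can be estimated directly in the subsample. Section 9.2.4 lists "proportional hazards models, Cox regressions, multivariate and logistic" among its methods. Logistic odds ratios tolerate selection on outcome alone. Incidence, relative risks and hazard ratios do not, unless the sampling is accounted for.

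**Working it through.** **1. The plan's own count.** 200 people × 2 specimen types = 400 per evaluation time, and 100 people × 2 = 200 per periodontal group. Both match Section 3.3.2, so the specimen budget fits a 100 + 100 draw on periodontitis and leaves nothing for baseline sampling of anyone else.

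**2. Can the outcome rule act at baseline?** At entry nobody has hypertension (3.4.1). Baseline specimens come only from people already selected (5.1), 400 in number (3.3.2). Selection therefore precedes any outcome. The outcome rule could work only if baseline specimens from the whole cohort were stored and chosen from later. Section 4 leaves that open; 3.3.2 and 5.1 point against it.

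**3. Inputs for size (Section 3.3.1).** Relative risk 2.4, 10% with periodontitis, incidence 21.5%, dropout 40%. The text does not make clear which group the 21.5% describes, so three readings are carried.

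**4. Expected hypertension cases under the 100 + 100 draw.** Cases = 100 × p1 + 100 × p0, with p1 = 2.4 × p0.

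| Reading of 21.5% | p1 | p0 | Cases in 200 | After 40% dropout (× 0.6) |
|---|---|---|---|---|
| Risk with periodontitis | 0.215 | 0.215/2.4 = 0.0896 | 21.5 + 9.0 = 30.5 | 18.3 |
| Overall cohort risk | 0.4526 | 0.215/(0.9 + 0.1 × 2.4) = 0.1886 | 45.3 + 18.9 = 64.1 | 38.5 |
| Risk without periodontitis | 0.516 | 0.215 | 51.6 + 21.5 = 73.1 | 43.9 |

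Risks, relative risk and odds ratio by periodontitis all remain estimable under this draw.

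**5. Baseline specimens missing if cases were instead chosen later from the whole cohort.** With 10% periodontitis, 1,212 people give 121.2 with and 1,090.8 without. A baseline draw of 100 without periodontitis covers 100/1,090.8 = 9.2% of them. On the first reading, 1,090.8 × 0.0896 = 97.7 cases without periodontitis are expected in the cohort, and 100 × 0.0896 = 9.0 of them would have a baseline specimen. About 91% would not. The fraction is the same on all three readings; dropout is ignored.

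**6. Distortion if selection were on outcome.** The counts here are assumptions; the protocol gives none. First reading throughout.

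- *100 cases and 100 non-cases.* Cohort risk = 0.1 × 0.215 + 0.9 × 0.0896 = 0.102. Share with periodontitis = 0.0215/0.102 = 0.211 in cases and 0.0785/0.898 = 0.087 in non-cases. Apparent incidence is 50% rather than about 10%. Unweighted relative risk = [21.1/(21.1 + 8.7)] / [78.9/(78.9 + 91.3)] = 0.707/0.464 = 1.52 instead of 2.4. The odds ratio stays at 2.78.
- *Four equal cells.* 200/4 = 50 each, so relative risk and odds ratio are both 1.0 by construction. If the four cells were the evaluated groups, 50 falls short of the plan's own bound of about 100. Meeting it would take 400 people and 800 specimens per time.

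**The case against.** The strongest reply is that the last sentence only describes the end-of-follow-up sample. The umbrella cohort follows people until they develop hypertension (3.2.1), those diagnosed elsewhere are asked to complete an end-of-study visit (3.6.1.2), and people who stay on antihypertensive therapy are eliminated (3.4.3). A sentence confirming that both those who became hypertensive and those who did not are sampled would make sense there, and its tense fits. The four cells would then be what the 100 + 100 sample becomes, not strata to be filled. This reading is plausible and is the one the fix adopts. But the sentence says where sampling will be done, names no time, and sits in the section that sets the sample, so staff could implement either rule.

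A reader might go further and infer that the plan fixes the periodontitis-hypertension association by design. The document does not support that. The only counts it sets are on periodontitis; none is given for hypertension. The figures of 1.52 and 1.0 in the working depend on quotas assumed for illustration. The main association is sized and estimated in the 1,212-person cohort, outside the subsample. Nor is the absence of sampling weights from Section 9.2.4 a fault: that section lists families of methods, and weighting can be left to an analysis plan.

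It is also fair to say that the periodontitis draw does not keep the natural joint distribution either, since it raises periodontitis from the planned 10% to 50%. That is harmless for comparisons made within or conditional on periodontitis group.

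**Conclusion.** The contradiction stands. Section 3.3.2 gives two selection bases, and the outcome-based one cannot choose people for baseline sampling as Sections 3.4.1 and 5.1 are written. Its consequences are conditional. If the outcome rule were implemented, baseline specimens would be missing for most hypertension cases without periodontitis, and unweighted incidence, relative risks and hazard ratios in the subsample would be distorted. Only if the four cells were filled to quotas would the subsample's periodontitis-hypertension association be set by design.

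The effect is confined to the 200-person subsample. That subsample carries the primary endpoint and the goal linking baseline microbiome to incident hypertension, and the loss of specimens would be irreversible, so the matter should be settled before baseline sampling. The sizes rest on Section 3.3.1's planning values, with the 21.5% read three ways.

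**What to change.** 1. In Section 3.3.2, state that the subsample is drawn at baseline on periodontitis status only, 100 + 100.
2. Reword the last sentence so that the four hypertension-by-periodontitis cells are analysis groups formed at the end of follow-up, with the exit visit of those who develop hypertension counting as their end-of-follow-up sample.
3. Reconcile Sections 4 and 5.1 on whether baseline saliva and plaque are taken from everyone or only from the 200.
4. Acknowledge that the hypertension group will be far below about 100 (roughly 30 to 73 cases before dropout, 18 to 44 after), so the network argument supports the periodontitis comparison but not one by hypertension status.

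Items 1, 2 and 4 cost only wording, and so does item 3 if baseline sampling is confined to the 200. If outcome-based selection is what the investigators want, the price is higher: baseline specimens collected and stored from up to 1,212 people, stated cell counts and sampling fractions, and an analysis weighted for them.
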